###### Mathematical fluency test

2.5.2.3.4

Immediately after the end of the cognition tests, a mathematical fluency test was carried out by means of test number 6 of the Woodcock protocol (52). In this test, participants were given a three-minute period to perform as many simple mathematical calculations as possible.

##### Psychological health

2.5.2.4

Health status was assessed using the adapted version for children and adolescents of EuroQol five dimensions three level (EQ-5D-Y-3 L) questionnaire (53). This questionnaire evaluates health status across five dimensions: (i) mobility; (ii) self-care; (iii) usual activities; (iv) pain/discomfort and (v) anxiety/depression. Participants rate their level of difficulty or problems in each dimension using a Likert-type scale with three response options: (i) no problem, (ii) some problems, and (iii) many problems. Additionally, the questionnaire included a visual analog scale (VAS) to gauge general health, where participants assigned a score between 0 and 100 to indicate their current perception of overall health. Furthermore, self-perceived health was assessed using the classic self-reported health item (54). Participants categorize their health as either “excellent” (5); “very good” (4); “good” (3); “fair” (2); and “poor” (1).

##### Motivational variables

2.5.2.5

###### Novelty need satisfaction scale

2.5.2.5.1

It evaluated novelty (55). Five of the 19 questions that make up the original scale were selected. Participants were asked to rate their agreement with these five statements on a Likert-type scale, with following levels: (1) “strongly disagree”; (2) “disagree”; (3) “neither agree nor disagree”; (4) “agree”; and (5) “strongly agree.”

###### The Spanish version of the sport satisfaction instrument

2.5.2.5.2

It evaluated enjoyment and boredom (56) in general studies. This scale consists of eight items measuring intrinsic satisfaction, with two subscales: satisfaction/enjoyment (five items) and boredom (three items). Participants rate their agreement with the items related to fun or boredom on a five-point Likert-type scale, with following levels: (1) “strongly disagree”; (2) “disagree”; (3) “neither agree nor disagree”; (4) “agree”; and (5) “strongly agree.”

###### School climate

2.5.2.5.3

School climate was assessed by Students’ Perception of School Climate scale (PACE-33) (57). For this study, we used four indicators: “Student-teacher relationships” (4 items), “physical safety” (4 items), “group cohesion” (4 items) and “methodological resources” (3 items). Participants rate their agreement with each item on a five-point Likert scale, with following levels: (1) “strongly disagree”; (2) “disagree”; (3) “neither agree nor disagree”; (4) “agree”; and (5) “strongly agree.”

##### School leaders’, teachers’ and students’ perception about the suitability and the implementation of PAL, AB, and AR

2.5.2.6

To gather qualitative information on the implementation of the multicomponent intervention and analyze the process, individual interviews were conducted with the participating teachers and school leaders. Additionally, focus groups with students were organized, adhering to the guidelines outlined in Finn and McInnis’s study (58). This way, useful information was obtained such as perceptions, limitations, strengths, areas for improvement, perceived benefits, enjoyment, motivation, training needs, fidelity and sustainability, from the perspective of the stakeholders who have been directly involved in the intervention. The interviews and focus groups were facilitated by the same researchers across all study provinces and were exclusively conducted in experimental centers. For the interviews, 1 school leader and a group of 4–5 teachers per center, who were involved in and familiar with the intervention, were selected. All interviews were conducted individually. These individual interviews were semi-structured, lasting approximately 30 min each, and were audio recorded for analysis. The focus groups, comprising 6–8 students selected (heterogeneous profiles), were also semi-structured and last around 30–40 min. Similar to the interviews, they were audio recorded to ensure accurate documentation of insights. The interviews were fully transcribed for the subsequent analysis of the data obtained from them.

#### Confounding variables

2.5.3

##### Sociodemographic characteristics

2.5.3.1

The socioeconomic status of participants was assessed using the Spanish-adapted version III of The Family Affluence Scale (FAS III) (59). This scale comprises six questions concerning the purchasing level of the participant’s family. Each question is rated on a categorical scale, and the total score, derived from the sum of responses across all six items, yields an aggregate index ranging from 0 to 13.

##### Dietary patterns

2.5.3.2

Adherence to the Mediterranean diet was evaluated using the updated version 2.0 of the KIDMED questionnaire (60). The KIDMED 2.0 questionnaire comprises 16 questions that participants respond to. These questions encompass both positive and negative aspects related to the Mediterranean diet. Participants’ scores are calculated based on their responses, and the scores are categorized into three levels: (i) ≥ 8, indicating optimal adherence to the Mediterranean diet; (ii) = 4–7, suggesting a need for greater adherence to the Mediterranean diet; and (iii) ≤ 3, indicating low adherence to the Mediterranean diet.

### Data analysis

2.6

Continuous variables will be presented as mean and standard deviation or median and interquartile range, as appropriate, while categorical variables will be expressed as frequency and percentage. A cross-sectional approach will be utilized, employing descriptive, correlational, regression, and differential analyses, along with Structural Equation Modeling. To evaluate the effects of the interventions on outcomes, repeated measures analysis will be conducted, with outcome measures serving as dependent variables in separate models, the intervention as an independent variable, and controlling for potential confounders (i.e., gender). Non-parametric analyses will be conducted if normality analyses indicate non-normal distributions. Quantitative analyses will be conducted using the SPSS v.29.0 statistical package (IBM, Armonk, NY, United States), with a confidence level of 95%.

Additionally, qualitative data from semi-structured interviews and focus groups will be analyzed using NVIVO software (61). Content analysis strategies will be employed, involving two phases: a deductive phase aimed at identifying information relevant to the study’s objectives, followed by an inductive phase focused on identifying teachers’ and students’ experiences, thoughts, and reflections related to AR, AB, and PAL (62).

To mitigate potential biases associated with the quasi-experimental design, we will apply statistical adjustments to control for confounding variables (i.e., gender, city, socioeconomic status) and ensure the robustness of our findings. Additionally, sensitivity analyses will be conducted to assess the impact of potential biases.

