**Methods:**

A quasi-experimental study was conducted with the aim to involve a total of 800 students aged 12–14 years old from 11 schools (7th and 8th grade) in south-western Spain, five schools forming the intervention group and six schools forming the control group. The evaluation included two independent measurements: pre-intervention and post-intervention. The intervention lasted 29 weeks and consisted of a multi-component programme including a weekly PAL, two 5 min daily AB, and a daily AR. Primary outcomes included accelerometer-based PA and sedentary time, health-related physical fitness, academic indicators, and executive functions. For statistical analyses, descriptive, correlational, regression, and repeated measures ANOVA analyses will be applied. Additionally, qualitative data were gathered through semi-structured individual interviews and focus groups, and information will be evaluated with thematic analysis.

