### Participants and selection criteria

2.2

Participants in the MOVESCHOOL study were apparently healthy adolescents from secondary schools in the regions of Caceres and Cadiz (Spain). The MOVESCHOOL study established the following inclusion criteria for participants: (i) enrolled in 7th or 8th grade (12–14 years old); (ii) without any physical disabilities or health issues that could restrict PA levels; and (iii) having parental or legal guardian consent to participate in the study. Additionally, we included three criteria for schools: (i) having at least 60 students in 7th and 8th grade; (ii) not involved in any other PA or health promotion programs; and (iii) located within a 50-kilometre radius of the research group’s centers in Cadiz and Caceres.

Figure 1 illustrates the flow diagram of the participants recruitment process. Seven schools in Caceres and four schools in Cadiz were selected to participate through a letter of invitation addressed to the school administration. A meeting was held with the school management teams of the selected schools, to explain the study and obtain their consent. Two study groups were established through a nonequivalent control group design: (i) intervention group and (ii) control group. In Cadiz, two intervention groups and two control groups were assigned; and in Caceres, three intervention groups and four control groups were assigned. Each group corresponds to a different school. All 7th and 8th grade students at the participating schools who provide their informed consent were invited to participate in the study. The parents of these students received an information document detailing the study, the inclusion criteria, the informed consent process, and an invitation to attend an information meeting at the school. For students to participate in the study, their parents or guardians had to sign the informed consent form along with the student’s consent.

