**Figure 1 fig1:**
[figure not shown]
Flow diagram of study participants.

The recruitment process was designed to achieve 800 participants (400 per group), which guarantees to detect small sized effects with an *α* error of 0.001 and a power (1 − *β*) of 0.95, even with an experimental dropout rate of 15% (GPower 3.1.9.4, Düsseldorf, Germany). To establish this sample size, Love et al. (38) were referenced, as they found an average effect size <0.1 for our main variable, MVPA time during the school day.

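### Whole schools were allocated, but the intervention effect is to be tested by a student-level repeated measures ANOVA with no school term; if schools differ in their pre-post change, the standard errors are too small

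*Protocol article*

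**What the plan says.** **Allocation.** Section 2.2 of the protocol article states that "Two study groups were established through a nonequivalent control group design". It continues: "In Cadiz, two intervention groups and two control groups were assigned; and in Caceres, three intervention groups and four control groups were assigned". It then adds: "Each group corresponds to a different school". The Abstract gives the same totals: "five schools forming the intervention group and six schools forming the control group". The unit of allocation is therefore the school, and there are 11 of them.

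**Analysis.** The Abstract says that "descriptive, correlational, regression, and repeated measures ANOVA analyses will be applied". Section 2.6 says for the intervention effects that "repeated measures analysis will be conducted, with outcome measures serving as dependent variables in separate models, the intervention as an independent variable". It names gender as a confounder there, and gender, city and socioeconomic status in its last paragraph. The confidence level is 95%. The article mentions no school or class effect, multilevel model, cluster-robust error, ICC or design effect. The promised sensitivity analyses concern potential biases, not correlation within schools.

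**Sample size.** Section 2.2 counts students only: "The recruitment process was designed to achieve 800 participants (400 per group"), for small effects, with 15% dropout allowed.

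**The concern.** In a pre-post design with two groups, the repeated measures ANOVA test of group by time is a two-sample t-test on individual changes. It treats every student as an independent observation of the intervention effect. Here the contrast is carried by 11 schools, so a comparison of school means has 11 - 2 = 9 degrees of freedom.

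Stable differences between schools cancel out of the change. Differences between schools in the change itself do not. Such differences are plausible here. Each experimental school has its own technician (section 2.4), active breaks are timed with each school's management (2.3.2), active recess is prepared with the school's own PE teachers (2.3.3), and marks are reported by each school (2.5.2.3.3).

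The same kind of model is meant for every quantitative outcome, including school-day MVPA, the main variable. The source cited for the sample size found an average effect below 0.1 on that variable, so even modest school-level noise matters.

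**Working it through.** **1. The plan's own figure.** Section 2.2 gives 800 students, an alpha "error of 0.001 and a power" of 0.95, and 15% dropout. It states neither a numerical effect size nor a pre-post correlation. The closest standard variant is the G*Power within-between interaction with f = 0.10 and rho = 0.5 (both assumed), where lambda = f² × N × 2/(1 - rho).

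- Required N is 616 (lambda = 0.01 × 616 × 4 = 24.64, power 0.951). After dropout this is 616/0.85 = 725, against 800 stated.
- At 800 × 0.85 = 680 completers, lambda = 27.2 and power is 0.972.

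The 800 is not reproduced exactly, but under this variant it meets the stated power as a lower bound. No variant tried contains a clustering term.

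**2. Inputs for the error rate.** From the article: 11 schools (5 v 6), 680 completers, two-sided 5% (from the 95% confidence level). Assumed: the school ICC of change, shown from 0 to 0.10.

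**3. Formula.** Mean school size m = 680/11 = 61.8. Design effect DE = 1 + (m - 1) × ICC. The standard error should be √DE times the student-level one. Actual type I error = 2 × [1 - Φ(1.96/√DE)].

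Example at ICC 0.02: DE = 1 + 60.8 × 0.02 = 2.22; √DE = 1.49; 1.96/1.49 = 1.32; error = 18.8%.

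**4. Simulation under no effect.** Individual changes in 5 schools of 68 v 6 schools of 57, 20,000 runs per setting.

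| ICC of change | DE | SE should be × | Type I, formula | Type I, simulated |
|---|---|---|---|---|
| 0 | 1.00 | 1.00 | 5.0% | 5.2% |
| 0.005 | 1.30 | 1.14 | 8.6% | 8.6% |
| 0.01 | 1.61 | 1.27 | 12.2% | 12.7% |
| 0.02 | 2.22 | 1.49 | 18.8% | 19.1% |
| 0.05 | 4.04 | 2.01 | 33.0% | 33.4% |
| 0.10 | 7.08 | 2.66 | 46.1% | 46.9% |

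A separate simulation with 10,000 runs gave 11.9%, 18.7%, 33.5% and 46.7% at ICC 0.01, 0.02, 0.05 and 0.10. In these simulations a t-test on the 11 school mean changes rejected about 5% of the time throughout.

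**5. Power once schools are respected.** The variance of the difference in school means, in units of the SD of change, is [ICC + (1 - ICC)/68]/5 + [ICC + (1 - ICC)/56.7]/6. The test is a noncentral t on 9 df. Two effect sizes are shown because the article gives none. The 0.4 SD is the effect implied by the variant in step 1: setting N × d²/4 = 27.2 with N = 680 gives d = 0.4.

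| ICC of change | 0.2 SD, alpha 0.05 | 0.4 SD, alpha 0.05 | 0.4 SD, alpha 0.001 |
|---|---|---|---|
| 0.01 | 0.450 | 0.953 | 0.364 |
| 0.02 | 0.346 | 0.874 | 0.222 |
| 0.05 | 0.212 | 0.635 | 0.081 |
| 0.10 | 0.141 | 0.415 | 0.032 |

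At the article's own alpha of 0.001, the stated power of 0.95 is not reached at any of these ICCs.

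**The case against.** The strongest reply is that the article gives no ICC and that the relevant one, for change, could be close to zero because stable school differences cancel. That stands as a limit on size. At ICC 0 the test is correct, and at 0.005 the error rate is about 1.7 times nominal. A reader might infer that the false-positive rate simply is several times 5%; the documents do not support that without the condition.

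A second reply is that section 2.6 says only repeated measures analysis, which could be read as a mixed model, with details left to an analysis plan. The Abstract, however, says ANOVA. Section 2.6 also lists its model terms and confounders, and school is not among them. A mixed model with a student effect alone would have the same fault. This is a stated method that does not fit the allocation, not a detail left out.

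Third, the adjustment is not confined to student characteristics: city is included and may absorb some shared influences. It separates Cadiz from Caceres, but not the four schools in one or the seven in the other.

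A reader might also infer that ANOVA would delete students with one wave and so bias the result. The article states no rule for incomplete data, so that inference is not supported and forms no part of this point.

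**Conclusion.** The concern holds in conditional form. The stated analysis ignores the unit of allocation, and it must be corrected before the effects are estimated. If the school ICC of change is about 0.01, the nominal 5% test has an actual error rate of 12-13%; at 0.02 it is about 19%, at 0.05 about 33%, and at 0.10 about 47%. Only from about 0.01 to 0.02 upwards is the inflation several-fold. The figures rest on an assumed ICC, 680 completers and roughly equal school sizes within each arm. Any correlation within classes is left out. Non-random allocation does not remove the need for valid standard errors, and correct standard errors will not remove confounding between the non-equivalent groups.

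**What to change.** In section 2.6 and the Abstract, replace the student-level repeated measures ANOVA with one of these:

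- **(a) School-level analysis.** Compare school mean changes between groups, covariate-adjusted if wanted, on about 9 df, or about 8 if city is included.
- **(b) Linear mixed model.** Use random effects for school, school by time, and student, with group by time as the tested term and Satterthwaite or Kenward-Roger df. A school intercept alone is not enough, because it cancels from the change. City and covariates entered only as main effects cancel in the same way, so enter them with time interactions, or use ANCOVA on baseline. Report the school-mean test alongside. With 11 schools the school-by-time variance may be estimated as zero (a simple moment estimate was non-positive in 22% of simulated trials at ICC 0.01), and the model then falls back towards the student-level test.

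Restate the power claim in section 2.2 with an assumed ICC of change, a numerical effect size and its metric. State which alpha applies, since section 2.2 uses 0.001 and section 2.6 implies 0.05.

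The cost is revised wording and syntax, wider confidence intervals and a less favourable stated power. No new data are needed, and section 2.6 still describes the analyses as future work.

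### The effect analysis switches to non-parametric methods after a normality check, and the plan does not say how confounder adjustment survives the switch

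*Protocol article*

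**What the plan says.** Data analysis (2.6) gives each outcome its own repeated measures model, with "the intervention as an independent variable, and controlling for potential confounders (i.e., gender" as the only confounder listed at that point. The next sentence is the rule at issue: "Non-parametric analyses will be conducted if normality analyses indicate non-normal distributions". It names no normality test or level, does not say whether scores or residuals are examined, and names neither the replacement method nor how covariates enter it.

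The last paragraph of the same section ties adjustment to the quasi-experimental design: "we will apply statistical adjustments to control for confounding variables (i.e., gender, city, socioeconomic status". It also promises sensitivity analyses, which it does not specify.

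Participants and selection criteria (2.2) explains why adjustment matters here: "Two study groups were established through a nonequivalent control group design". There are five intervention and six control schools.

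The outcomes are mixed. Accelerometry, fitness and anthropometry are continuous. Screen time (2.5.1.1), engagement, learning perception, novelty, enjoyment and school climate are categories or short Likert scales. The EQ-5D-Y items have three levels: "Participants rate their level of difficulty or problems in each dimension using a Likert-type scale with three response options". Self-rated health has five.

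**The concern.** The rule is a decision that the plan states, not a detail left for later: the outcome of a preliminary check determines which analysis estimates the intervention effect. Two things follow.

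First, a formal normality test answers the wrong question at this sample size. With several hundred pupils it detects departures too small to disturb inference on means. It will also reject for discrete bounded scores whatever the quality of the model.

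Second, the commonest replacements (Mann-Whitney, Wilcoxon) take no covariates. If one of these is used, the comparison of non-equivalent schools loses the adjustment that the plan relies on to limit bias. Some outcomes would then be reported as adjusted mean differences and others as rank comparisons, with the choice made by the data.

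**Working it through.** **Sample size used.** The plan gives no figure for the switch rule itself. The relevant number is the target: "The recruitment process was designed to achieve 800 participants (400 per group", at an alpha "error of 0.001 and a power" "of 0.95, even with an experimental dropout rate of 15" per cent. Hence 800 × 0.85 = 680 analysed, or 340 per group.

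Whether 800 can be reproduced depends on an unstated correlation. For a two-group, two-time interaction with noncentrality f²·N·m/(1 − ρ), m = 2 and f = 0.1 (assumed metric), N is 616 at ρ = 0.5 and 738 at ρ = 0.4. Dividing by 0.85 gives 725 and 869, which bracket 800. The target is therefore taken as given.

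**Step 1: how often would a formal test trigger the switch?** Simulation at the 5% level (from the plan's 95% confidence level), 1,000 samples per cell. Outcome shapes are assumed because the protocol gives none; skewed data are gamma. Cells show rejection by Shapiro-Wilk / Kolmogorov-Smirnov with Lilliefors limits.

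| Assumed shape | n = 340 | n = 680 |
|---|---|---|
| Exactly normal | 4% / 5% | 4% / 5% |
| Skewness 0.2 | 25% / 15% | 47% / 25% |
| Skewness 0.3 | 50% / 29% | 81% / 51% |
| Skewness 0.5 | 92% / 63% | 99.7% / 92% |
| Skewness 0.8 | 100% / 96% | 100% / 100% |
| Nine-item 0–6 scale | 35% / 55% | 86% / 94% |
| Four- or five-item 1–5 scale | 100% / 100% | 100% / 100% |
| Single 1–5 item; seven-category screen time | 100% / 100% | 100% / 100% |

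At n = 800 the skewness 0.5 row is 100% / 94% and the nine-item row is 95% / 97%.

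**Step 2: what does the switch gain or cost?** Simulation with no intervention effect, n = 680, 2,000 runs per row. The change score is y = b·c + √(1 − b²)·e. The confounder c has unit variance and is shifted by the stated imbalance (in SD) in one group. The error e has unit variance and skewness 1. Cells show type I error at nominal 5%.

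| Imbalance | Slope b | Unadjusted Mann-Whitney | Adjusted linear model | Covariate-adjusted rank (Quade type) |
|---|---|---|---|---|
| 0 | 0.2 | 0.0465 | 0.043 | 0.0475 |
| 0 | 0.3 | 0.056 | 0.051 | 0.052 |
| 0.1 | 0.2 | 0.059 | 0.053 | 0.052 |
| 0.1 | 0.3 | 0.066 | 0.0455 | 0.044 |
| 0.2 | 0.2 | 0.086 | 0.048 | 0.0495 |
| 0.2 | 0.3 | 0.119 | 0.0585 | 0.0525 |
| 0.3 | 0.2 | 0.1225 | 0.049 | 0.0405 |
| 0.3 | 0.3 | 0.243 | 0.0485 | 0.048 |

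Monte Carlo standard error near 5% is √(0.05 × 0.95 / 2000) ≈ 0.005.

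**Step 3: hand check of the unadjusted column.** The spurious group difference is imbalance × b, and its standard error is √(2/340) = 0.0767.
- Imbalance 0.2, slope 0.2: 0.04 / 0.0767 = 0.52. The two-sided normal rejection rate is P(Z > 1.44) + P(Z < −2.48) ≈ 8.2%, against 8.6% simulated.
- Imbalance 0.3, slope 0.3: 0.09 / 0.0767 = 1.17. The rate is P(Z > 0.79) + P(Z < −3.13) ≈ 21.7%, against 24.3% simulated.

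The normal calculation is for a mean comparison, so exact agreement with a rank test on skewed data is not expected. The size is confirmed.

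**The case against.** The strongest reply is that the plan never says it will drop adjustment. It names no unadjusted test, its closing promise to adjust exempts no analysis, and a covariate-adjusted rank method would satisfy both sentences; in Step 2 such a method holds type I error at 4.1% to 5.3% for imbalances of 0.2 to 0.3 SD. The phrase about normality analyses could also mean inspection of residuals, in which case the Step 1 rates do not apply. A condensed article commonly leaves the choice of test and replacement to the analysis plan.

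Much of this stands. A reader might infer that adjustment will be abandoned for nearly every outcome, or that the plan contradicts itself. The documents support neither: the two commitments are unreconciled, not incompatible. The skewness of the main variable, school-day moderate-to-vigorous activity, is not given either, and at skewness 0.2 to 0.3 a formal test at n = 680 rejects in only 25% to 81% of samples.

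Two further inferences fail. Rank tests do not lose the group-by-time effect here: with only two measurements, a Mann-Whitney test on change scores is the rank analogue of that contrast. Nor can the rule be blamed for losing a mixed model or adjustment for school, since the plan contains neither. Leaving a Gaussian model for three- or five-level items is also no harm in itself; the problem is leaving it for an unspecified method.

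The reply does not rescue the rule. Making the main analysis conditional on a normality check is a stated choice, and it remains a poor one even if an adjusted rank method is intended, because the estimand would still vary between outcomes.

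**Conclusion.** The point holds as a badly fixed rule with an unresolved consequence. If the trigger is a formal test, it would fire for the short Likert, single-item and categorical outcomes and for continuous outcomes with skewness of about 0.5 or more, and unpredictably for milder skew. The switch is not needed to protect the error rate: with skewness 1 the adjusted linear model stays at 4.8% to 5.9% for imbalances of 0.2 to 0.3 SD. If the replacement is an unadjusted rank test, type I error rises to between 8.6% and 24.3% under the same imbalances and slopes of 0.2 to 0.3. At an imbalance of 0.1 SD it is only 5.9% to 6.6%.

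These figures rest on assumed outcome shapes, imbalance and slopes, and on independent pupils; clustering by school was not simulated. They show direction and rough size, not the error rate of this study. The analyses are described in the future tense, so the sentence can still be changed, and it should be.

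**What to change.** Delete the switch rule in Data analysis (2.6) and state instead:

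- The planned repeated measures model, adjusted for gender, city and socioeconomic status, is the single main analysis of each continuous or summed-scale outcome. Its assumptions are judged on residuals.
- Where residuals are clearly skewed, a transformation, bootstrap or named covariate-adjusted rank analysis of the same group-by-time contrast is reported as a sensitivity analysis only.
- The EQ-5D-Y items and self-rated health are analysed with ordinal models carrying the same covariates, whatever a normality check shows.

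The cost is a few sentences of text and slightly more modelling work, mainly for the ordinal outcomes. No additional data are needed.
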